## Abstract

**Background:**

Pain from injuries is one of the commonest symptoms in children attending emergency departments (EDs), and this is often inadequately treated in both the pre-hospital and ED settings, in part due to challenges of continual assessment and availability of easily administered analgesic options. Pain practices are therefore a key research priority, including within the field of paediatric emergency medicine. Methoxyflurane, delivered via a self-administered Penthrox® inhaler, belongs to the fluorinated hydrocarbon group of volatile anaesthetics and is unique among the group in having analgesic properties at low doses. Despite over 30 years of clinical acute analgesia use, and a large volume of evidence supporting its safety and efficacy, there is a paucity of randomised controlled trial data for Penthrox®.

**Methods:**

This is an international multi-centre randomised, double-blind, placebo-controlled phase III trial assessing the efficacy and safety of methoxyflurane delivered via the Penthrox® inhaler for the management of moderate to severe acute traumatic pain in children and young people aged 6–17 years. Following written informed consent, eligible participants are randomised to self-administer either inhaled methoxyflurane (maximum dose of 2 × 3 ml) or normal saline placebo (maximum dose 2 × 5 ml). Patients, treating clinicians and research nurses are blinded to the treatment. The primary outcome is the change in pain intensity at 15 min after the commencement of treatment, as measured by the Visual Analogue Scale (VAS) or the Wong-Baker FACES® Pain Rating scale, with the latter converted to VAS values. Secondary outcome measures include the number and proportion of responders who achieve a 30% reduction in VAS score compared to baseline, rescue medication requested, time and number of inhalations to first pain relief, global medication performance assessment by the patient, clinician and research nurse, and evaluation of adverse events experienced during treatment and during the subsequent 14 ± 2 days. The primary analysis will be by intention to treat. The total sample size is 110 randomised and treated patients per treatment arm.

**Discussion:**

The Methoxyflurane AnalGesia for Paediatric InjuriEs (MAGPIE) trial will provide efficacy and safety data for methoxyflurane administered via the Penthrox® inhaler, in children and adolescents who present to EDs with moderate to severe injury-related pain.

**Trial registration:**

EudraCT, 2016–004290-41. Registered on 11 April 2017.

ClinicalTrials.gov, NCT03215056. Registered on 12 July 2017.

**Electronic supplementary material:**

The online version of this article (10.1186/s13063-019-3511-4) contains supplementary material, which is available to authorized users.

## Background

Pain is the most common symptom in patients requiring emergency healthcare, with acute trauma frequently the cause [1, 2]. There are many short-term and long-term consequences of inadequately treated acute pain, and it is universally accepted that its management should begin at the earliest opportunity [3, 4]. In 2012, the Royal College of Emergency Medicine [5] identified pain management as the most popular indicator for quality of care in an emergency department (ED). Current standards recommend the simple and timely sequential process of pain recognition, assessment, measurement, therapeutic actions/interventions and reassessment [6]. Pain-relief regimes work optimally when effective analgesics are supported by formal protocols and guidelines underpinned by staff and patient education.

Patients with traumatic pain often receive inadequate analgesia in pre-hospital and ED settings [7, 8]. The reasons for this are multifaceted, but in children they likely include challenges such as assessment tool application, perceived competing clinical priorities, ease/route of drug administration, availability of therapeutic options and a limited evidence base. Paediatric emergency physicians have prioritised pain practices as a key research priority [9]. The ideal analgesic for acute pain should have rapid onset of action, act over an appropriate and predictable period of time, be well tolerated and be effective across a wide range of pain types in different populations. The time to clinical analgesic effect of oral or topical analgesics is too slow to meet the standards of treating trauma-related moderate or severe paediatric pain [10]. Intranasal or inhaled delivery of analgesic agents allows quick and simple drug administration without the distress of intravenous cannulation and may help improve the management of acute moderate to severe pain in children in pre-hospital and ED settings.

Methoxyflurane (2,2-dichloro-1,1-difluoro-1-methoxyethane) is a volatile fluorinated hydrocarbon [11]. It is a colourless liquid with a fruity odour. Methoxyflurane was first introduced as an inhalational anaesthetic in the 1960s. In the 1970s, due to availability of newer anaesthetic agents and case reports of dose-related renal tubular damage at high anaesthetic doses of long duration, its use was generally discontinued. However, unlike other fluorinated anaesthetics, methoxyflurane has analgesic properties at much lower doses, which are not associated with nephrotoxicity [12].

In Australia, methoxyflurane (Penthrox®) is licensed for short-term relief of acute pain in adults and children (including minor surgical procedures), and has been used for pain relief in sub-anaesthetic doses for over 30 years. The number of administrations has now exceeded 6 million, with only a single report of nephrotoxicity at recommended analgesic doses. There were confounding factors in this adult case report [13].

Methoxyflurane is available in 3-ml ampoules containing pure methoxyflurane to be used in a self-administered hand-held and portable Penthrox® inhaler, to a potential maximum recommended dose in 24 h of two 3-ml vials [14]. Methoxyflurane is absorbed rapidly, resulting in fast onset of analgesia, usually within 6–10 inhalations [14]. As a non-controlled drug, the preparation time between prescription and patient administration is quick, and Penthrox® likely requires less patient monitoring than opioid analgesics. Methoxyflurane administered via the Penthrox® inhaler may eliminate the need for opioid analgesia for dislocations or fractures, since the pain relief may be sufficient for reduction or splinting.

A literature review on the use of methoxyflurane in EDs and prehospital settings recommended that large, blinded, placebo-controlled studies investigating its analgesic efficacy should be conducted [15]. This was largely addressed in trial MEOF-001 (the STOP trial), conducted at six sites in the UK between 2011 and 2012 [16]. However, the majority of the participants were adults, with just 90 adolescent patients (aged 12–17 years) and no younger children. One other paediatric RCT showed that methoxyflurane was effective for the treatment of pain associated with upper limb fractures, but this trial included just 41 patients over the age of 5 years [17].

The Methoxyflurane AnalGesia for Paediatric InjuriEs (MAGPIE) trial—a well-powered, randomised, blinded, placebo-controlled trial—therefore aims to determine whether methoxyflurane is effective and safe in the treatment of moderate to severe injury-related pain in children and young people aged 6–17 years.

## Methods

### Aim

This trial aims to establish the efficacy and safety of methoxyflurane, when self-administered via the Penthrox® inhaler, in children and adolescents presenting to EDs with moderate to severe injury-related pain.

### Trial design

This is an international multi-centre, randomised, double-blind, placebo-controlled, explanatory phase III trial assessing the efficacy and safety of methoxyflurane delivered via the Penthrox® inhaler for the management of moderate to severe pain associated with minor trauma. Recruitment and randomisation are stratified by age group bandings of 6–8 years, 9–11 years and 12 to < 18 years in a 2:2:1 ratio. A trial flowchart is shown in Fig. 1.

**Fig. 1 Fig1:**
[figure not shown]
MAGPIE trial flowchart. ED emergency department, MAGPIE Methoxyflurane AnalGesia for Paediatric InjuriEs

Key trial events are outlined in Fig. 2.

**Fig. 2 Fig2:**
[figure not shown]
MAGPIE trial schedule of trial events. MAGPIE Methoxyflurane AnalGesia for Paediatric InjuriEs, UMSS University of Michigan Sedation Scale, VAS Visual Analogue Scale, WBF-PRS Wong-Baker FACES® Pain Rating scale

The protocol for this trial has been written in accordance with the Standard Protocol Items: Recommendations for Trials (SPIRIT) checklist (Additional file 1).

### Trial setting

Nine EDs within the UK and Ireland are participating, selected from the membership of Paediatric Emergency Research in the UK and Ireland (PERUKI) (www.peruki.org), a collaborative paediatric emergency medicine research network [18]. Participating sites may be tertiary or district general hospitals with EDs that treat either children alone or both children and adults. Site selection was based on several factors, including previous research experience, site research infrastructure and number of likely recruits estimated from a preparatory service evaluation.

### Trial participants

#### Inclusion criteria

The following inclusion criteria apply:Age ≥ 6 years to ≤ 17 years.Attending an ED following minor trauma.Pain scores (at screening and just prior to administration of study treatment) measuring between 60 and 80 mm on the Visual Analogue Scale (VAS) [19] or, where the patient is unable to understand the VAS, pain scores between 6 and 8 using the Wong-Baker FACES® Pain Rating scale (WBF-PRS).

#### Exclusion criteria

Patients are not enrolled to the trial if they meet any of the following criteria:Critical, life-threatening or limb-threatening condition requiring immediate management.Open fractures.Any other clinical condition that may, in the opinion of the Investigator, impact the patient’s ability to participate in the trial.Patient deemed not cognitively capable of effectively self-administering the trial treatment.Treatment with any analgesic agent within 5 h prior to presentation to the ED, with the exception of Entonox (50% nitrous oxide and 50% oxygen mixture, which is prohibited within 30 min prior to presentation to the ED), diclofenac (which is prohibited within 8 h prior to presentation to the ED) or oral morphine (which is prohibited within 10 h prior to presentation to the ED).Chronic pain.Receipt of an investigational medicinal product (IMP) in the preceding 3 months.Known pregnancy or breastfeeding females.Personal or familial hypersensitivity to methoxyflurane or any fluorinated anaesthetics.Requirement for oxygen therapy.Known or genetic susceptibility to malignant hyperthermia or a history of severe adverse reactions (ARs) in either patient or relatives.Clinically evident respiratory depression.Previous use of methoxyflurane (including as an IMP).History of signs of liver damage including after previous methoxyflurane use or halogenated hydrocarbon anaesthesia.Known significant renal impairment.Altered level of consciousness due to any cause including head injury, drugs or alcohol.Known significant cardiovascular disease (e.g. pathological arrhythmia).Inability to participate in telephone follow-up on day 14 (± 2 days).

### Primary outcome

The primary outcome is the change in VAS (including WBF-PRS scores subsequently converted to VAS values) at 15 min after the commencement of treatment.

### Secondary outcomes—efficacy

Number and proportion of participants in each arm who achieve a 30% reduction in VAS score at 15 min.Number and proportion of participants in each arm who achieve a 30% reduction in VAS score at 5, 10 and 20 min.Change in pain intensity (VAS) at 5, 10, 15, 20 and 30 min, and every 30 min thereafter until the point of ED discharge.Number and proportion of participants in each arm requesting rescue medication within 20 min of start of treatment, and any time during treatment.Time to requesting rescue medication.Time to first-reported analgesic effect.Number of inhalations until first-reported analgesic effect.Whether the patient covered the dilutor hole in the inhaler during inhalation.Global medication performance assessment by patient, clinician and research nurse, using a 5-point Likert scale.

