### Administration of trial treatments

The research nurse provides training in the use of the device to the patient using a demonstration inhaler which contains no IMP and supports them in its use as necessary for the duration of IMP administration. Baseline vital signs (heart rate, blood pressure, respiratory rate and oxygen saturation) are measured along with an assessment of baseline sedation level using the University of Michigan Sedation Scale (UMSS) [20].

After randomisation, the baseline (time = 0) pain score is assessed, to ensure relative stability of pain intensity. If the baseline pain score has fallen outside the range of 60–80 mm on the VAS or 6–8 on the WBF-PRS, the patient is withdrawn from the trial (randomised but not treated).

If successfully randomised, the research nurse assists the participant to self-administer 10 successive inhalations of the IMP. Participants and parents/legal guardians are advised that rescue analgesia is available immediately on request at any time. Permitted rescue medications are intranasal fentanyl, intranasal diamorphine, intranasal ketamine, intravenous morphine, oral morphine or Entonox (50% nitrous oxide and 50% oxygen mixture), dependent on the standard practice of the participating site and at the discretion of the treating clinician. This approach is in line with current recommended practice [10] for the management of moderate to severe pain. Standard-of-care oral analgesic medications (paracetamol and ibuprofen) may be administered as concomitant medications alongside rescue medication. Participants who report pain relief due to IMP inhalation are advised to continue to self-administer additional inhalations, as required, during their ED attendance.

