#### Pain scores

Pain intensity is re-assessed using the VAS or WBF-PRS at 5, 10, 15, 20 and 30 min after the start of inhalation of the trial treatment, and every 30 min thereafter until ED discharge. Additional unscheduled pain scores are assessed at the time of any other key events, such as during any injury treatment, prior to rescue medication administration, prior to premature trial withdrawal or just prior to ED discharge.

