#### Statistical analysis plan

The primary analysis shall be an intention-to-treat (ITT) analysis of the difference between methoxyflurane and placebo on the VAS, to include all patients who are randomised and receive trial treatment and undergo at least one post-baseline efficacy assessment. A pragmatic conversion of WBF-PRS scores to VAS scores (e.g. WBF-PRS 2 = VAS 20 mm, WBF-PRS 4 = VAS 40 mm, etc.) will be completed. The primary model will be an analysis of covariance (ANCOVA) of the VAS at 15 min following the start of inhalation of trial treatment with baseline pain as covariate, treatment and age group as fixed effect and site as random effect using the ITT population. The treatment effect shall be estimated as the average difference between the methoxyflurane-treated group and the placebo group at 15 min. Pain scores taken after the initiation of a rescue medication will be included in the primary analysis. This approach is conservative for the primary analysis and allows for patients with missing data at any time point to be included in the analysis with less bias than if patients are dropped from the analysis. Sensitivity analysis of primary endpoint pain values shall be performed using Worst Observation Carried Forward (WOCF). To exclude the possibility that conversion of any WBF-PRS scores (ordinal scale) into VAS scores (continuous scale) significantly influences the outcome of the trial, sensitivity analysis using a non-parametric test (Wilcoxon rank-sum test) will be performed.

Various methods will be used for secondary endpoint analyses. For treatment comparison of change from baseline for continuous variables with more than one measurement within a time period, repeated-measures analysis employing restricted maximum likelihood (REML)-based mixed-model repeated measures (MMRM) will be used. For continuous variables with baseline value and one post-baseline measurement, ANCOVA will be used, unless specified otherwise. Least square means (LSmeans), SE, LSmeans difference, 95% confidence interval (CI) and *p*-value will be presented. Logistic regression analyses adjusted for baseline will be performed for the binary variables, and the odds ratio and 95% CI for the odds ratio of treatment group comparisons will be given.

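### The 30% responder outcomes carry no condition on rescue, so read literally a patient rescued before the time point can count as a responder to the inhaler

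*Protocol article*

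**What the plan says.** **Outcome definition.** Under Secondary outcomes—efficacy, the article lists "Number and proportion of participants in each arm who achieve a 30% reduction in VAS score" at 15 min, and likewise those who "achieve a 30% reduction in VAS score at 5, 10 and 20 min". The score at the time point is the only criterion.

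**Rescue.** Administration of trial treatments states that "rescue analgesia is available immediately on request at any time". The permitted agents are "intranasal fentanyl, intranasal diamorphine, intranasal ketamine, intravenous morphine, oral morphine or Entonox". The Discussion adds that the treating clinician reviews the patient at 20 min with rescue in mind, so earlier rescue depends on a request.

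**Analysis.** The Statistical analysis plan section says: "Pain scores taken after the initiation of a rescue medication will be included in the primary analysis". It calls this conservative for that analysis. Binary variables get logistic regression adjusted for baseline, with nothing said about rescue. A worst-observation-carried-forward (WOCF) sensitivity analysis is planned for the primary endpoint, without saying whether it applies to rescued patients.

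**Data collected.** Requests for rescue within 20 min and time to requesting rescue are separate secondary outcomes. Under Pain scores, an unscheduled score is taken "prior to rescue medication administration".

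**Aim.** Trial design describes the study as a "double-blind, placebo-controlled, explanatory phase III trial".

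**The concern.** A responder proportion is normally read as the share of patients for whom the study treatment worked. Here a child on saline could ask for rescue at, say, 8 min, receive an opioid, ketamine or nitrous oxide, and have a score 30% below baseline at 15 min. By the definition as written, that child is a placebo responder, although the inhaler had failed. A trial that describes itself as explanatory is not well served by this.

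At stake is the size of the responder difference. If the less effective arm needs more early rescue, its responder proportion is raised by the rescue drugs, and the contrast shrinks. The outcome would then mix response to the inhaler with response to rescue, and the definition alone would not let a reader separate the two.

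**Working it through.** **1. The plan's own figure.** The article gives no figure for the responder outcomes. Its stated power (at least 95% for 13.3 mm, SD 27.1 mm, 110 per arm) concerns the primary endpoint. At an assumed two-sided 5% level it reproduces: 95.3% by the normal approximation, 95.2% by the noncentral t. It does not bear on this point.

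**2. The threshold.** Eligible baseline scores are 60 to 80 mm, so a 30% reduction is a fall of 0.30 × 60 = 18 mm to 0.30 × 80 = 24 mm.

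**3. Formula.** For each arm let
- R = proportion with at least a 30% reduction and no rescue before the time point,
- r = proportion rescued before the time point,
- q = share of rescued patients who are at or past the threshold at the time point (taken as equal in both arms).

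The score-only responder proportion is R + q·r. With subscripts M for methoxyflurane and P for placebo, the score-only difference is

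(R_M − R_P) − q·(r_P − r_M).

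The dilution relative to a definition that counts rescued patients as non-responders is therefore q·(r_P − r_M). It is zero if the rescue proportions are equal, and small if both are small.

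**4. Numbers.** The article gives none of R, r or q, so all of these are assumptions. With q = 0.5:
- rescue 10% placebo, 2% active: 0.5 × (10 − 2) = 4 points;
- rescue 20% placebo, 5% active: 0.5 × (20 − 5) = 7.5 points.

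**5. Effect on a comparison with 110 per arm.** Assume R_P = 30% and R_M = 50%. With rescued patients as non-responders, the difference is 20 points and power is 86.2%. With the score-only definition, over q = 0.3 to 0.7:

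| Rescue before time point, placebo / active | Difference (points) | Power |
|---|---|---|
| 5% / 1% | 18.8 to 17.2 | 81% to 74% |
| 10% / 2% | 17.6 to 14.4 | 76% to 58% |
| 20% / 5% | 15.5 to 9.5 | 64% to 29% |
| 10% / 10% | 20.0 | about 85% |

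For example, at 10% / 2% with q = 0.5: placebo 30 + 0.5 × 10 = 35%, active 50 + 0.5 × 2 = 51%, difference 16 points.

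**6. What limits the size.** To alter the 15-min outcome, rescue must be requested, given and take effect within 15 min, and the clinician's review comes only at 20 min. The 5- and 10-min outcomes leave less time still.

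**The case against.** The strongest reply is that the article never says a rescued patient is a responder. The inclusion sentence names only the primary analysis, no sentence classifies rescued patients for the binary outcomes, and the full protocol or the SAP, neither of which is shown, may settle it. That stands in part: a reader might infer that the trial has adopted a rule of crediting rescue to the inhaler, and the documents do not support this. They do support something narrower. The published definition has no rescue condition, and applied literally it counts such a patient.

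Second, rescue requests are reported by arm beside the responder proportions, so an imbalance would be visible. True, but that does not correct the proportions. Third, a score-only responder with rescue shown separately is a legitimate outcome. Also true, which is why it should be kept as a sensitivity analysis.

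Fourth, the direction is benign: more rescue on placebo shrinks the difference and creates no false benefit. That stands, and it lowers the priority.

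A reader might also infer that the primary analysis is faulty, or that its power is materially reduced. The article does not support this. Including post-rescue scores is a disclosed and reasoned choice, in keeping with its intention-to-treat approach. There are no rescue rates or rescue effects from which to compute a loss. The adolescent effect assumption comes from interim data of an earlier trial, and the article does not say whether those data already included post-rescue scores. Nor can one say that no planned analysis deals with rescue, because the scope of the WOCF analysis is not stated.

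**Conclusion.** The point holds in a limited form. The responder outcomes at 5, 10, 15 and 20 min are defined by the pain score alone while rescue is open throughout, so a rescued patient can be counted as a responder to the inhaler. If early rescue is commoner on placebo, the responder difference is diluted against methoxyflurane. If rescue is equal between arms or rare before 15 min, the effect is small.

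The size of 4 to 7.5 points rests wholly on assumed early rescue of 10-20% on placebo and 2-5% on active, with half of those patients reaching the threshold. The power figures rest in addition on assumed responder proportions of 30% and 50%. They illustrate and do not predict. Since the endpoint is secondary and the likely bias runs against the drug, this is a cheap improvement to consider and no threat to the main conclusion.

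**What to change.** Before unblinding:

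- Define a responder at each time point as a patient with at least a 30% VAS reduction from baseline and no rescue medication started before that time point. Patients rescued earlier count as non-responders.
- Keep the score-only version as a sensitivity analysis.
- Leave the primary analysis as planned.
- Add one supplementary 15-min analysis that uses the recorded pre-rescue score for patients rescued before 15 min, or state that the planned WOCF analysis treats them in this way.

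The cost is wording and a little programming. Rescue timing and pre-rescue scores are already recorded, and conduct of the trial does not change. The downside is that the responder outcome becomes a composite of pain reduction without rescue and should be described as such.
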